### 2.6. Ancillary neurophysiological and biomarker assessments

DREAMER incorporates ancillary assessments to generate mechanistic and trial-readiness information beyond vPSG [17].

The coordinating center will perform transcranial magnetic stimulation (TMS) in participants with isolated RSWA and in an appropriate comparison group without RSWA. TMS will assess cortical excitability and inhibitory/facilitatory intracortical mechanisms. The aim is to determine whether isolated RSWA is associated with early cortical neurophysiological changes analogous to those described in RBD or early synucleinopathy [18].

The Cagliari center will perform cervical, masseter, and ocular vestibular-evoked myogenic potentials when feasible. These measures provide information on brainstem pathways that may be relevant to REM atonia regulation and early RBD-related neurophysiology [19]. Startle response assessment may also be included according to the final harmonized protocol.

The Bologna and San Raffaele centers will perform brainstem auditory evoked potentials in selected participants with isolated RSWA and matched comparators without RSWA. These measures will complement other neurophysiological assessments of brainstem function.

Blood samples will be obtained whenever possible, with priority given to participants with isolated RSWA. Samples will be processed and stored for future proteomic, metabolomic, and glycomic analyses. The purpose is to determine whether isolated RSWA is associated with peripheral molecular signatures overlapping with those previously described in isolated RBD [20,21].

Brain magnetic resonance imaging, computed tomography, dopamine transporter imaging, or other investigations will not be mandated by the protocol, but may be performed when clinically indicated as part of routine diagnostic work-up. Results will be recorded in the eCRF when available.

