### 2.9. Sample size and recruitment assumptions

DREAMER uses a pragmatic recruitment target based on expected RSWA frequency and feasibility within participating centers. Previous quantitative work in adults without RBD showed that isolated RSWA elevations may be detected in a substantial minority of individuals, with approximately 14% of patients without dream-enactment behavior reaching previously established RBD-level RSWA thresholds [4,7]. Therefore, the initial recruitment target is > 500 participants over 18 months, expected to yield approximately 85 individuals with isolated RSWA. Because the DREAMER population is restricted to adults aged ≥40 years, and because RSWA becomes more frequent with age, the number of isolated RSWA cases may exceed this estimate.

The initial 24-month phase is not designed as a definitive phenoconversion trial. Instead, it is designed to assemble an enriched cohort and collect the standardized baseline data required for adequately powered follow-up. Recruitment assumptions will be reassessed after the first 6 months of enrollment. If the observed frequency of isolated RSWA or the rate of technically classifiable vPSG recordings is lower than expected, recruitment targets may be increased, and the comparator strategy may be adjusted by selecting an age- and sex-matched subgroup without RSWA for long-term follow-up.

Assuming approximately 85 participants with isolated RSWA and long-term follow-up over 5 years, the study may observe a sufficient number of incident RBD events to generate preliminary estimates of relative risk compared with participants without RSWA. These estimates will be used to plan future prevention or neuroprotection trials rather than to support immediate clinical implementation.

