### 2.11. Statistical analysis plan

Baseline characteristics will be summarized for the overall cohort and stratified by RSWA status. Continuous variables will be reported as mean and standard deviation or median and interquartile range, according to distribution. Categorical variables will be reported as counts and percentages.

Participants with isolated RSWA will be compared with participants without RSWA. Continuous variables will be analyzed using Student’s t test or Mann-Whitney U test, as appropriate. Categorical variables will be analyzed using chi-square or Fisher’s exact tests. Effect sizes and confidence intervals will be reported whenever possible to avoid overreliance on significance testing.

RAI will be analyzed both as a continuous variable and as a categorical classification variable. Multiple linear regression will evaluate associations between RAI and clinical, pharmacological, sleep, and neurophysiological predictors. Logistic regression will evaluate predictors of isolated RSWA status. Candidate covariates will include age, sex, antidepressant exposure, neurological comorbidity, sleep apnea severity, REM sleep duration, and participating center.

For long-term follow-up, cumulative incidence of RBD will be described using Kaplan-Meier methods. Cox proportional hazards models will estimate the association between baseline isolated RSWA and incident RBD, adjusted for age, sex, medication exposure, center, and relevant sleep-disorder comorbidities. Competing-risk methods may be considered for incident neurodegenerative outcomes or death. Sensitivity analyses will evaluate the influence of antidepressant exposure, minimum REM duration, comorbid sleep apnea, and alternative RAI thresholds.

The extent and pattern of missing data will be reported. If missingness is limited, complete-case analyses will be used. If missingness is substantial and plausibly missing at random, multiple imputation may be considered for regression models. Follow-up attrition will be summarized and compared between RSWA and non-RSWA groups.

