### 2.12. Study status and timeline

The DREAMER study was registered at ClinicalTrials.gov before completion of recruitment. Ethics approval was obtained on 24 January 2024, and participant recruitment started on 22 February 2024. At the time of submission of this Study Protocol, participant recruitment is still ongoing and has not yet been completed, although the recruitment phase is close to completion. Recruitment is expected to be completed by 30 June 2026.

Completion of participant recruitment will be followed by baseline data verification, RAI computation, classification of participants according to the predefined RSWA/RAI criteria, identification of the isolated RSWA subgroup, and selection of the comparator group without RSWA according to the prespecified matching strategy. Therefore, the analytical cohort has not yet been constituted, and no study results have yet been generated, analyzed, or reported.

After completion of recruitment, baseline data validation, and analytical cohort constitution, the longitudinal follow-up phase will begin and will continue for 5 years. Follow-up data collection is expected to be completed approximately by 30 June 2031. Baseline descriptive and feasibility results are expected only after completion of recruitment, database verification, RAI-based classification, comparator-group selection, and database lock, approximately by September–December 2026. Final longitudinal analyses of incident REM sleep behavior disorder and neurodegenerative outcomes are expected after completion of the planned 5-year follow-up period, approximately by late 2031 or early 2032.

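### Sections 2.9, 2.11 and 2.12 disagree on whether comparators are matched and which participants enter the baseline RSWA/RAI analyses, and the matched BAEP comparison has only unpaired tests

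*Protocol article*

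**What the plan says.** - **Models (Section 2.11).** The predictors of interest include age and sex: "Logistic regression will evaluate predictors of isolated RSWA status. Candidate covariates will include age, sex, antidepressant exposure, neurological comorbidity, sleep apnea severity, REM sleep duration". Participating center completes the list. A multiple linear regression of RAI on clinical, drug, sleep and neurophysiological predictors is also planned. No analysis set is named for either model.
- **Group tests (Section 2.11).** "Continuous variables will be analyzed using Student’s t test or Mann-Whitney U test, as appropriate". Categorical variables get chi-square or Fisher tests. All of these take the groups as independent.
- **Analytical cohort (Section 2.12).** After RAI classification comes "selection of the comparator group without RSWA according to the prespecified matching strategy. Therefore, the analytical cohort has not yet been constituted". On timing: "Baseline descriptive and feasibility results are expected only after completion of recruitment, database verification, RAI-based classification, comparator-group selection, and database lock".
- **Matching factors (Section 2.9).** Age and sex are named once, in case RSWA frequency or the rate of classifiable recordings falls short: "the comparator strategy may be adjusted by selecting an age- and sex-matched subgroup without RSWA for long-term follow-up".
- **Ancillary tests (Section 2.6).** Bologna and San Raffaele will record "brainstem auditory evoked potentials in selected participants with isolated RSWA and matched comparators without RSWA", with the matching factors not named. TMS is to be done "in participants with isolated RSWA and in an appropriate comparison group without RSWA", with no mention of matching.

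**The concern.** Secondary objectives 2 and 3 (Section 2.1) ask how participants with and without isolated RSWA differ and which characteristics go with RAI. The answer depends on how the participants without RSWA enter the analysis.

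Taken literally, Section 2.12 yields a cohort made of every participant with RAI below 0.85 plus a matched subset of the rest. If matching is on age and sex, the two groups have the same age and sex distribution by construction. A test of either as a predictor then reflects the selection. The Introduction names age and sex as influences on RSWA, and Section 2.9 says RSWA becomes more frequent with age, so a null result would be misleading. The linear model has a further problem: isolated RSWA is defined by RAI, so sampling on RSWA status is sampling on that model's own dependent variable.

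For BAEPs, Section 2.6 itself specifies matched comparators, yet no planned group test uses the matching.

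**Working it through.** **1. What the plan's own figures allow.** The plan gives no power, alpha or effect size for any baseline comparison, so there is no such figure to reproduce. Its only sample-size figures are a target above 500, about 85 isolated RSWA cases and a frequency near 14%. These do not multiply exactly (500 × 0.14 = 70; 85 / 0.14 = 607; 85 / 500 = 17%). That is a separate matter and does not bear on this point. The check below uses 500 participants and 17% cases.

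**2. The sections side by side.**

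| Question | 2.9 | 2.11 | 2.12 |
|---|---|---|---|
| Is the comparator group matched? | Only if recruitment assumptions fail | Not mentioned | Yes, by a prespecified strategy |
| On what? | Age and sex | – | Not named |
| For which analyses? | Long-term follow-up | Overall cohort for descriptive summaries; not stated for tests and models | The analytical cohort; baseline results come after selection |

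**3. Consequence if the matched cohort is used.** Cohorts of 500 were simulated, with 600 to 1,000 runs per scenario. A latent severity score stood in for RAI, with the top 17% as cases. Each case was matched 1:1 to the nearest-age participant of the same sex within 5 years. Assumed effects in SD units were age 0.35 per 10 years, sex 0.30 and antidepressant 0.50; a weaker set used 0.20, 0.20 and 0.30. The documents give no effect sizes, caliper or ratio, so all of these are assumptions.

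| Quantity | All participants | Matched 1:1 | Change |
|---|---|---|---|
| Logistic coefficient, age per 10 years | 0.64 | 0.03 | removed |
| Same, weaker effects | 0.36 | 0.01 | removed |
| Unpaired t test on age, rejection rate | 99.9% | 0% | – |
| Same, weaker effects | 80% | 0% | – |
| Linear slope on age | 0.351 | 0.157 | 1 − 0.157/0.351 = 55% smaller |
| Same, weaker effects | 0.197 | 0.081 | 59% smaller |
| Linear slope on sex | 0.299 | 0.131 | 56% smaller |
| Linear slope on antidepressant | 0.503 | 0.576 | 0.576/0.503 = 15% larger |
| Same, weaker effects | 0.294 | 0.355 | 21% larger |
| Logistic coefficient, antidepressant | 0.88 | 0.90 | essentially none |

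With 2:1 matching the logistic age coefficient goes from 0.63 to 0.05, and the linear age slope shrinks by 46% (0.352 to 0.189). A separate simulation with other assumptions (3-year caliper, different RAI scaling) gave 58-64% shrinkage of the linear age slope and 45-52% inflation of an unmatched slope. The direction of the inflation is stable; its size is not.

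For a null covariate in the 1:1 matched set, type I error at nominal 5% was 3.7-5.7% in the logistic model and 4.2-5.2% in the linear model, both with age and sex included.

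**4. The BAEP comparison.** If matching induces a within-pair correlation ρ, the true variance of the mean difference is (1 − ρ) times what the unpaired test assumes. In large samples its true level is 2 × [1 − Φ(1.96 / √(1 − ρ))].

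- ρ = 0.1: 1.96 / 0.949 = 2.07, level 3.9%.
- ρ = 0.3: 1.96 / 0.837 = 2.34, level 1.9%.

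Here ρ is the share of the marker's variance that the matching factors explain. A marker correlating 0.3 with age has ρ = 0.3² = 0.09 from age matching; the level is then 4.0% by the formula and 4.2% in the simulation.

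For power, assume 42 pairs (two of four centers, about half of 85) and a true difference of 0.5 SD. Simulation gives 63% unpaired against 65% paired at ρ = 0.1, and 64% against 76% at ρ = 0.3.

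**5. RAI regressed on BAEPs.** Section 2.6 limits BAEPs to selected cases and matched comparators. Table 2 gives isolated RSWA priority and tests others as feasible. Either way, who has a BAEP depends on RAI, so a regression with RAI as outcome is fitted to a sample selected on its outcome.

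**The case against.** The strongest reply is that the baseline analyses were never meant for a matched set. Section 2.11 opens with the overall cohort, Section 2.7 reports frequency among enrolled participants, and Table 2 collects history, medication, vPSG and RAI on everyone. Listing age and sex as candidate predictors also fits a full-cohort analysis. Section 2.12 is a timeline, and Sections 2.2 and 2.8 use the comparator group for follow-up. On that reading none of the effects in step 3 arises.

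This stands as a possible reading, and probably the better design. It does not settle the text: the overall-cohort phrase covers only the descriptive summaries, and Section 2.12 explicitly makes comparator selection part of constituting the analytical cohort.

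A reader might infer that age and sex will certainly be reported as unrelated to RSWA. The documents do not support that, because the models are not tied to the matched set and those two factors are named only conditionally. A reader might also infer that the planned tests have generally wrong error rates. They do not: the unpaired tests err only on the conservative side, and only for markers related to the matching factors, while the adjusted models hold close to 5%.

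Matching ratio and variables may be in a fuller document, and their absence here is no fault. The BAEP work is described as exploratory, and effect sizes and intervals are favored over tests. That lowers the stakes, but intervals that ignore the matching are also too wide.

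**Conclusion.** The point holds as a conflict between sections with a conditional consequence, plus a smaller mismatch for BAEPs.

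- **Conflict.** Sections 2.9 and 2.12 differ on whether matching is contingent or prespecified. Sections 2.11 and 2.12 leave open whether baseline analyses use all classifiable participants or the matched cohort.
- **If the matched cohort is used and matching is 1:1 on age and sex.** Both are removed as predictors of isolated RSWA. Linear RAI slopes on them shrink by roughly 55-60% (somewhat less at 2:1), and other linear slopes are inflated by about 15-50%. Logistic coefficients for non-matching variables are essentially unaffected.
- **BAEPs.** The comparators are matched as the plan stands, and the listed group tests ignore it. The cost is conservatism and lost power that grow with the variance explained by the matching factors. It is slight at a within-pair correlation of 0.1 and about 12 power points at 0.3 (76 − 64). Both correlations are assumed. RAI regressions on BAEPs also rest on a sample selected on RAI.

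This should be settled before the analytical cohort is constituted, which Section 2.12 says has not yet happened.

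**What to change.** 1. Reconcile Sections 2.9 and 2.12 on whether matching is planned or contingent, and on which factors.
2. State in Sections 2.11 and 2.12 that the baseline frequency estimate, the group comparisons and the RAI/RSWA regressions use all RAI-classifiable participants. Reserve the matched comparator set for the ancillary tests and follow-up.
3. In matched subsets, including BAEPs, compare groups with a model that has the matching factors as covariates. A paired or matched-set analysis is the alternative where pairs exist, but it drops incomplete pairs. For RAI and BAEP associations, make the marker the outcome and RAI the predictor, with the matching factors as covariates. In simulation with age and sex as the factors, this stayed within 7% of the full-cohort slope.
4. Do not test or interpret the matching factors as predictors in any matched subset.

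The cost is wording only. The core baseline data and RAI are already collected on all enrolled participants, and no results have been generated.

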### 2.7. Outcomes

The main outcomes of the 24-month cohort-construction phase are:

Number of participants screened, eligible, enrolled, and classifiable by RAI.Frequency of isolated RSWA among enrolled participants.Completeness and quality of vPSG, clinical, neurophysiological, and biosample data.Feasibility of harmonized multicenter eCRF-based data capture.Recruitment rate and retention readiness for long-term follow-up.

The primary long-term clinical outcome is incident RBD, defined by development of clinical dream-enactment behavior with vPSG evidence of RSWA according to accepted diagnostic criteria.

Secondary long-term outcomes include:

Change in RAI over time, when repeat vPSG is available.Development of subthreshold dream-enactment behavior or increased RBD questionnaire scores.Diagnosis of Parkinson disease, dementia with Lewy bodies, multiple system atrophy, or other neurodegenerative disorders.Association between baseline RAI and neurophysiological markers.Association between baseline RAI and blood-based proteomic/metabolomic/glycomic signatures.Attrition, loss to follow-up, and feasibility of repeated annual assessment.

The procedures used to identify and confirm these outcomes during follow-up are described below.

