### 2.8. Follow-up procedures and phenoconversion ascertainment

Participants classified as having isolated RSWA and a comparator group without isolated RSWA will be invited to participate in longitudinal follow-up. Follow-up will be performed at least annually by in-person visit, telephone interview, video consultation, or review of clinical records, according to participant availability and local center procedures. The follow-up strategy is designed to detect two clinically relevant forms of phenoconversion: conversion to clinically manifest RBD and conversion to a neurodegenerative disorder within the alpha-synucleinopathy spectrum, in line with longitudinal evidence from isolated RBD cohorts and biomarker-based models of conversion risk [2,3].

At each follow-up contact, participants will be asked about the occurrence of new dream-enactment behavior, vocalizations or complex motor behaviors during sleep, sleep-related injuries, falls from bed, violent or disruptive sleep behaviors, and changes in sleep quality. Whenever possible, information will also be obtained from a bed partner, caregiver, roommate, or other reliable informant. Follow-up assessments will also record changes in medication exposure, especially antidepressants, benzodiazepines, melatonin, dopaminergic medications, antipsychotics, and other drugs potentially influencing REM sleep muscle tone or parasomnia expression. New diagnoses of sleep disorders, neurological disorders, psychiatric disorders, and relevant systemic illnesses will be recorded.

Incident RBD will be suspected when new recurrent dream-enactment behavior or other clinically relevant REM sleep-related motor behaviors are reported by the participant or an informant. In these cases, participants will be invited to undergo repeat full-night laboratory video-polysomnography, including chin electromyography and video documentation, whenever feasible. Incident RBD will be defined by the emergence of clinical dream-enactment behavior together with polysomnographic evidence of RSWA, according to accepted diagnostic criteria [1,22]. For each suspected or confirmed case, the date of first reported symptoms, date of clinical recognition, and date of polysomnographic confirmation will be recorded separately.

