Phenoconversion to neurodegenerative disease will be assessed through annual clinical history, neurological review, and documentation of any new diagnosis of Parkinson disease, dementia with Lewy bodies, multiple system atrophy, or other relevant neurodegenerative disorders, using established diagnostic frameworks where applicable [23–25]. Follow-up data collection will include symptoms or signs suggestive of parkinsonism, cognitive decline, visual hallucinations, fluctuating cognition, autonomic dysfunction, gait impairment, olfactory impairment, and other non-motor manifestations potentially relevant to prodromal synucleinopathy, consistent with research criteria and updates for prodromal Parkinson disease [26,27]. This approach is also supported by longitudinal application of prodromal Parkinson disease criteria in RBD cohorts [28].

When clinically indicated, participants will be referred for neurological evaluation and additional investigations according to local clinical practice, including neuropsychological testing, autonomic assessment, brain imaging, dopamine transporter imaging, or other biomarker investigations. These tests are not mandated by the protocol but will be recorded when available.

All suspected phenoconversion events will be reviewed by the recruiting center and, when necessary, discussed centrally by the study investigators. Outcome adjudication will use predefined criteria and will distinguish between no conversion, possible RBD, confirmed RBD, possible neurodegenerative phenoconversion, and confirmed neurodegenerative diagnosis. For longitudinal analyses, the event date will be defined as the earliest reliable date of symptom onset when available; otherwise, the date of clinical diagnosis or polysomnographic confirmation will be used. Participants who cannot be contacted will be classified as lost to follow-up after repeated contact attempts, and the date of last available assessment will be recorded.

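### Section 2.11 fixes Kaplan-Meier for cumulative RBD incidence without firmly treating death as a competing event, which slightly overstates that incidence

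*Protocol article*

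**What the plan says.** Section 2.7 of the protocol article sets the endpoint: "The primary long-term clinical outcome is incident RBD, defined by development of clinical dream-enactment behavior with vPSG evidence of RSWA". Neurodegenerative diagnoses are a separate, secondary outcome in the same section.

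Section 2.11 assigns the methods. For description, "cumulative incidence of RBD will be described using Kaplan-Meier methods". For association, "Cox proportional hazards models will estimate the association between baseline isolated RSWA and incident RBD", with covariate adjustment. The next sentence reads: "Competing-risk methods may be considered for incident neurodegenerative outcomes or death".

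Section 2.8 tracks two conversions separately: "conversion to clinically manifest RBD and conversion to a neurodegenerative disorder within the alpha-synucleinopathy spectrum". Adjudication sorts participants into "no conversion, possible RBD, confirmed RBD, possible neurodegenerative phenoconversion, and confirmed neurodegenerative diagnosis". The section asks for RBD symptom, recognition and confirmation dates, an event date for conversions, and the last assessment date for those lost to follow-up. It names neither vital status nor date of death.

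On duration, section 2.12 says that "the longitudinal follow-up phase will begin and will continue for 5 years".

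**The concern.** Kaplan-Meier treats a censored participant as still at risk of the event at some later time. That is reasonable for someone who moves away. It is not reasonable for someone who has died. If deaths are censored, one minus Kaplan-Meier estimates the RBD risk in a hypothetical population in which nobody dies. The actual cumulative incidence, which is the quantity section 2.11 names, can only be equal or lower.

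The competing-risk sentence does not settle the matter. It can mean that neurodegenerative disease and death are themselves the outcomes to be modelled, in which case RBD has no competing-risk provision. Or it can mean that they compete with RBD, in which case the plan recognises the problem but still names Kaplan-Meier and leaves the remedy to later discretion. Neither reading commits the RBD curve to an estimator of actual incidence.

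What is at stake is the absolute 5-year RBD incidence reported for each group. The error is systematic and one-directional, so more participants would not remove it.

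**Working it through.** **Inputs from the protocol article.** Follow-up T = 5 years (section 2.12); about 85 participants with isolated RSWA (section 2.9); age 40 or older (section 2.4). It gives no RBD incidence and no death rate, so there is no figure of its own to reproduce.

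**Assumptions.** Constant yearly hazards: r for RBD (1%, 2%, 5%, 10%) and c for death without RBD (0.5%, 1%, 2%). No other loss to follow-up.

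**Formulas.**
- One minus Kaplan-Meier, deaths censored: 1 − exp(−rT)
- Actual cumulative incidence, the Aalen-Johansen target: r/(r + c) × [1 − exp(−(r + c)T)]
- Approximate standard error of the 5-year estimate p: √[p(1 − p)/85]

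**One case in full: r = 2%, c = 1% per year.**
- 1 − exp(−0.10) = 9.52%
- (0.02/0.03) × [1 − exp(−0.15)] = 0.667 × 0.1393 = 9.29%
- Difference 0.23 points; ratio 9.52/9.29 = 1.025
- Standard error √(0.0952 × 0.9048/85) = 3.18 points

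**All cases.** Entries are percentages, with the overstatement in points in parentheses (differences taken before rounding).

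| r per year | 1 − KM | Actual, c = 0.5% | Actual, c = 1% | Actual, c = 2% | SE, n = 85 |
|---|---|---|---|---|---|
| 1% | 4.88 | 4.82 (0.06) | 4.76 (0.12) | 4.64 (0.23) | 2.34 |
| 2% | 9.52 | 9.40 (0.12) | 9.29 (0.23) | 9.06 (0.45) | 3.18 |
| 5% | 22.12 | 21.86 (0.26) | 21.60 (0.52) | 21.09 (1.03) | 4.50 |
| 10% | 39.35 | 38.90 (0.45) | 38.46 (0.89) | 37.60 (1.75) | 5.30 |

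The relative overstatement is about 1.2% at c = 0.5%, 2.3% to 2.5% at c = 1%, and 4.6% to 5.0% at c = 2%. It depends mainly on the death rate and hardly on the RBD rate. The largest overstatement in the table, 1.75 points, is about a third of its standard error (1.75/5.30 = 0.33) and equals about 1.5 of 85 participants.

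**Stress case.** With r = 10% and c = 5% per year, the figures are 39.35% against 35.18%. The 4.17 points are still below the standard error of 5.30.

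**The case against.** The strongest reply is that the point is immaterial. Kaplan-Meier is used only to describe incidence, the association analysis is the Cox model, and the error is smaller than sampling noise. Section 2.9 also says that later trials will be planned from preliminary relative-risk estimates, not from absolute incidence. Most of this stands, and it limits the weight of the point. It does not make Kaplan-Meier the right estimator of the quantity named.

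A second reply is that section 2.11 already mentions competing risks and death. Death is not a listed outcome in section 2.7, so reading it as an event that competes with the study outcomes is natural. That is fair, but the provision is only permissive, whereas Kaplan-Meier is stated without qualification. This is a choice the article makes, not detail left to an analysis plan that is not shown.

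A reader might go further in three ways that the article does not support:

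- **That a neurodegenerative diagnosis also precludes RBD.** Sections 2.7 and 2.8 define incident RBD by dream enactment plus RSWA on vPSG, according to accepted criteria. They state no requirement that neurodegenerative disease be absent, and nothing ends RBD follow-up at such a diagnosis. It competes only if the target is RBD before neurodegenerative disease. Section 2.1 does speak of RBD with subsequent neurodegenerative outcomes, which hints at that target but does not fix it.
- **That the group contrast is seriously distorted because the isolated RSWA group is older.** Section 2.12 refers to a prespecified matching strategy, section 2.9 raises age and sex matching conditionally, and the Cox model adjusts for age. Even with 5-year competing risks of 10% in one group and 5% in the other, and RBD risk of 10%, the overstatements are 1.053 and 1.025. The incidence ratio would shift by under 3% (1.053/1.025 ≈ 1.027).
- **That the Cox analysis is invalid.** With deaths censored, it estimates a cause-specific hazard ratio, which is a legitimate target.

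**Conclusion.** The point holds for death, as a modest one. Following section 2.11 as written censors deaths and reports a 5-year RBD incidence slightly above the actual one. The direction is certain whenever anyone dies without RBD. The size, about 1% to 5% relative, rests on assumed death rates of 0.5% to 2% per year and constant hazards. It is below one standard error with about 85 participants in every case examined, so no conclusion of this study is likely to turn on it.

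Two gaps go with it. The article does not say how RBD recorded after a neurodegenerative diagnosis is handled. And section 2.8 does not name the date of death, which is the one item the correct estimator needs for the one undisputed competing event. It would be too strong to infer that neurodegenerative conversion must be treated as competing, or that the comparison of RBD hazards between groups is compromised.

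**What to change.** In section 2.11:
- State that cumulative incidence of RBD will be estimated by the Aalen-Johansen method, with death without RBD as a competing event. This replaces both the Kaplan-Meier wording and the optional provision as far as RBD is concerned.
- Label the Cox estimate for isolated RSWA as a cause-specific hazard ratio.
- State whether RBD recorded after a neurodegenerative diagnosis still counts as an event. Treat that diagnosis as a competing event only if the intended target is RBD before neurodegenerative disease. This changes what is being estimated, so it should be a deliberate choice and not a by-product of the software.

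In section 2.8, add vital status and date of death to the follow-up data.

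The cost is a few sentences, one extra follow-up field and standard software. The reported incidence will be slightly lower. By section 2.12 the analytical cohort has not been constituted and longitudinal follow-up has not begun, so the change can be made now without any influence from outcome data.
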